**Methods/design:**

The study design consists of a prospective randomised controlled three-armed clinical trial, which will be carried out at a specialist clinic for integrative medicine, to investigate the clinical effects of hydrotherapy on osteoarthritis of the knee or hip joint, in comparison with conventional physiotherapy.

One hundred and eighty patients diagnosed with osteoarthritis of hip or knee will be randomly assigned to one of three intervention groups: hydrotherapy, physiotherapy, and both physiotherapy and hydrotherapy of the affected joint. In the first group, patients will receive Kneipp hydrotherapy daily, with water applied in the form of alternate cold and warm thigh affusions (alternating cold and warm water stimulation is particularly relevant to the knee and hip regions).

Patients in the second group will receive physiotherapy of the hip or knee joint three times a week. Patients in the physiotherapy-hydrotherapy combination group will receive both joint-specific physiotherapy three times a week and alternate cold and warm thigh affusions every day. Follow-up assessments will be on three levels: clinical assessment by the investigator; subjective patient assessment consisting of a patient diary, and questionnaires on admission and at the end of the treatment phase; and a final telephone assessment by the external evaluation centre. Assessments will be made at baseline, after two weeks of inpatient treatment, and finally after a further ten weeks of follow-up. The primary outcome measure will be pain intensity of the affected joint in the course of inpatient treatment, judged by the patient and the investigator. Secondary outcomes include health-related quality of life and joint-specific pain and mobility in the course of the study. Statistical analysis of the results will be on an intention-to-treat basis.

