### Sample size

On the basis of the data from the pilot study, carried out between June 2008 and January 2009 at the Kneipp Clinic in Bad Wörishofen, Germany, on 30 patients with pre-existing osteoarthritis of the hip or knee, a sample size was estimated using G-Power 3.0.10 software (Faul F, Erdfelder E, Lang A.-G, and Buchner A, 2007). According to this calculation, a sample size of n = 180 patients will suffice to determine a possible interaction between the groups with respect to the primary outcome, with a statistical power of 95%.

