### Statistical analysis

The data will be analysed using SPSS 15.0 (SPSS inc., 2006) software according to the intention-to-treat principle. Accordingly, all patients with valid values will be included in such a way that they remain in the groups in which they were originally randomised, irrespective of the treatment they actually received.

To check the homogeneity of the groups, a cross-sectional comparison of the baseline characteristics will be carried out. Various statistical procedures will be applied, depending on the scale level in each case. A factorial analysis of variance (one way ANOVA), if necessary with appropriate post hoc tests, will be carried out for the metric variables, body mass index (BMI), age and blood pressure, the scale values in SF-36, AIMS 2-F, visual analogue scale (VAS), and Lequesne index, the time required in the timed "up and go" test, and flexion and extension in the neutral-zero testing,. The nominal variables sex, affected joint (left, right, both sides) and the items of the EQ-5D will be analysed with chi-square tests. An analysis of variance with measured value repetition (ANOVA, repeated measures) will be performed for the longitudinal analysis of the primary outcome measure (VAS), and for the secondary outcome criteria (current mental health state, SF-36 sum scales, AIMS 2-SF scales, Lequesne index, time required in the timed "up and go" test, flexion and extension in the neutral-zero testing, and blood pressure) which are also metric variables. Should, contrary to expectations, there be any inhomogeneity between the groups with respect to important variables (baseline characteristics), adjustments will be made as far as possible in the scope of the longitudinal analysis. The secondary outcome measures on the nominal data level (EQ-5D) will be analysed with chi-square tests.

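### The primary repeated-measures ANOVA is a complete-case test with no end-of-stay arm contrast, yet it is described as intention-to-treat; a baseline-adjusted mixed model would serve better

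*Protocol article*

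**What the plan says.** The Statistical analysis section of the protocol article names both method and analysis set. On method: "An analysis of variance with measured value repetition (ANOVA, repeated measures) will be performed for the longitudinal analysis of the primary outcome measure (VAS"). On the set: "all patients with valid values will be included in such a way that they remain in the groups in which they were originally randomised", whatever treatment they received. The article presents this as following from intention-to-treat, and the abstract repeats the claim: "Statistical analysis of the results will be on an intention-to-treat basis". The software is SPSS 15.0.

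The Sample size section shows which effect is meant: "a sample size of n = 180 patients will suffice to determine a possible interaction between the groups" on the primary outcome, "with a statistical power of 95" per cent.

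Other relevant points in the article:
- The primary outcome is pain during the two-week inpatient stay, rated by the patient in a diary and by the investigator. The investigator rates twice, at admission and at the final examination. The text does not say how often the diary scale is filled in, and the schedule figure is not shown.
- Post hoc tests are mentioned only with the one-way ANOVA that compares the arms at baseline.
- Adjustment for baseline is made only if the arms turn out to differ.
- Research questions 5 and 6 ask how hydrotherapy compares with physiotherapy, and how hydrotherapy alone compares with the combination.

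**The concern.** Intention-to-treat has two parts: patients are analysed in the arm to which they were randomised, and all randomised patients are included. The plan keeps the first. Classical repeated-measures ANOVA undermines the second, because a patient with one missing rating contributes nothing, not even the ratings that were obtained. Patients may withdraw at any time, so incomplete series are foreseeable. If the reason for missing ratings is related to pain, the comparison is biased as well as less precise.

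The tested quantity is also a poor match to the questions. With three arms, the group-by-time interaction is an omnibus test of whether the mean profiles are parallel. A significant result does not say which arm has less pain at discharge, or by how much. Making baseline adjustment conditional on observed imbalance gives up precision that is available in every case.

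**Working it through.** **Inputs from the article.** N = 180, power 95%, three arms, two investigator ratings, two-week inpatient phase.

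**Assumptions.** Alpha 0.05; 60 patients per arm; 1% to 5% of values missing per rating, independently; m = 2 ratings (as for the investigator) or m = 14 (a daily diary).

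**1. The plan's own figure.** For a between-within interaction the test is a non-central F with

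λ = f² · N · m / (1 − ρ), df = (k − 1)(m − 1) and (N − k)(m − 1), k = 3.

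The article gives no f, ρ, m or alpha, so 180 cannot be reproduced. It is attainable: f = 0.15, m = 2 and ρ = 0.5 give N = 177. I therefore take 95% at N = 180 as given and ask what deletion does to it.

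**2. Patients left after deletion.** Complete rows = 180 · (1 − q)^m, where q is the proportion missing per rating.

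**3. Power left.** For 95% power at N = 180, λ must be 15.71 with m = 2 (df 2 and 177) or 34.00 with m = 14 (df 26 and 2301, sphericity assumed). With N′ complete patients, λ′ = λ · N′/180. This does not depend on ρ.

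| q | m = 2: N′ | λ′ | power | m = 14: N′ | λ′ | power |
|---|---|---|---|---|---|---|
| 1% | 176 | 15.36 | 94.5% | 156 | 29.47 | 90.5% |
| 2% | 173 | 15.10 | 94.2% | 136 | 25.69 | 84.6% |
| 3% | 169 | 14.75 | 93.6% | 118 | 22.29 | 77.1% |
| 5% | 162 | 14.14 | 92.6% | 88 | 16.62 | 59.8% |

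Independent missingness is the worst case for deletion. If gaps cluster within a few patients, fewer rows are lost.

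**4. Baseline adjustment, two ratings, nothing missing.** The interaction is then a test of change, with variance 2(1 − ρ)σ². Adjusting for baseline gives (1 − ρ²)σ². The ratio is 2/(1 + ρ): 1.54, 1.33 and 1.18 at ρ = 0.3, 0.5 and 0.7. Take arm means at discharge of 0, 0.25 and 0.5 SD. The between-arm sum of squares is 60 · (0.25² + 0.25²) = 7.5.

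| ρ | λ, interaction | power | λ, baseline-adjusted | power |
|---|---|---|---|---|
| 0.3 | 7.5/1.4 = 5.36 | 53% | 7.5/0.91 = 8.24 | 72% |
| 0.5 | 7.5/1.0 = 7.50 | 68% | 7.5/0.75 = 10.00 | 81% |
| 0.7 | 7.5/0.6 = 12.50 | 89% | 7.5/0.51 = 14.71 | 94% |

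Both are omnibus three-arm tests, so like is compared with like.

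**5. Daily diary, by simulation.** 1,000 runs per setting, 14 days, linear divergence to arm means of 0, 0.3 and 0.6 SD, correlation 0.5 + 0.5 · 0.7^lag, values missing completely at random at 0%, 2% or 5% per day:
- Sphericity-corrected (Greenhouse-Geisser) interaction on complete cases: power 0.73, 0.62, 0.39.
- Baseline-adjusted omnibus test on the last day: 0.92, 0.92, 0.89.
- With no true effect, the uncorrected interaction test rejects in 12% to 13% of runs; the corrected test rejects in about 5% to 6.5%.

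**The case against.** Several stronger readings are tempting, and the document does not support them.

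- *The analysis is not intention-to-treat.* Too absolute. Patients are analysed as randomised, and the mixed model proposed here also omits patients with no post-baseline value. What fails is inclusion of randomised patients with partial data.
- *A missed telephone call removes a patient from the primary analysis.* It cannot. The call comes ten weeks after the stay and covers questionnaires; the primary outcome is inpatient pain. Missed calls touch only the secondary outcomes measured at three visits.
- *The test spreads over a large number of degrees of freedom and has an inflated type I error.* This needs a daily diary and an uncorrected test. Daily rating is plausible, since the nursing staff enter blood pressure in the diary each day, but it is not stated for pain. With two ratings the interaction has 2 df and sphericity is no issue. Nothing says that a correction would be withheld.
- *Choosing an interaction forfeits the stated 95%.* The trial was sized for an interaction, so that choice alone costs nothing against the stated figure. The loss against 95% comes from deletion.
- *A focused pairwise contrast shows the full gain.* One unadjusted pairwise comparison with 85% to 88% power falls to about 73% to 78% after Bonferroni adjustment for three contrasts. That is why the comparisons above are omnibus against omnibus.
- *Early leavers are likely poor responders.* The document offers no evidence for this. The pilot reported no disqualification because of adverse reactions, though it says nothing about diary completeness.

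It can also be said that a condensed article leaves missing-data handling, sphericity correction and follow-up contrasts to the full protocol or analysis plan, and that listwise deletion is not written here. That is fair for details that are absent. It does not cover the method and analysis set that the article does state: an unseen plan would have to replace them, or add imputation, to remove the problem.

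**Conclusion.** The point holds in a limited form. The stated method, in its standard form, gives a complete-case analysis within the randomised arms and an omnibus test that does not estimate the arm differences behind questions 5 and 6.

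With two ratings, deletion is a small matter: at most about 2.4 points of power (95% to 92.6%) at 5% missing per rating. The larger cost there is the lack of routine baseline adjustment, 5 to 20 points of power in the illustration, depending on the correlation. With a daily diary, deletion itself becomes serious: 24 of 180 patients are lost at 1% missing per rating and 92 at 5%, with power down to about 90.5% and 60%.

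These figures rest on assumed missingness, independent gaps, alpha 0.05 and equal arms; the power figures for 14 ratings also assume sphericity. The direction holds under either diary reading; the size does not. No figure is available for bias. Severity: should be fixed. Confidence: moderate.

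**What to change.** Replace repeated-measures ANOVA for pain with a likelihood-based mixed model containing arm, time, arm-by-time and baseline pain, the last always included. Use all available ratings from every randomised patient with at least one post-baseline value. Name the arm differences at the end of inpatient care as the primary estimates, with multiplicity control over the pairwise contrasts. Use the same model for the secondary outcomes measured at three visits, where missed telephone calls matter. Describe the set as all randomised patients with available data, analysed as randomised. State how often the diary scale is completed.

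The cost is slightly more programming and an assumption about the covariance of the ratings. No new data are needed. One limit: where there are only two ratings, the model cannot recover a patient with no discharge rating, and its gain comes from the baseline adjustment.

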### Research questions

1. Does Kneipp hydrotherapy show a measurable effect in the sense of altered clinical findings in the affected knee or hip joint?

2. How effectively does hydrotherapy influence the clinical parameters of pain, range of movement, and function of the affected joint?

3. How effectively does hydrotherapy affect the secondary outcome measures of quality of life, pain experienced, mood, and blood pressure?

4. Do hydrotherapeutic applications simply provide short-term therapeutic success or are there long-term changes in the clinical findings?

5. Are the clinical effects of hydrotherapy comparable with those of conventional physiotherapy of the affected joint?

6. Are the clinical effects of hydrotherapy used as monotherapy comparable with a combination of hydrotherapy and physiotherapy of the affected joint?

7. Do unwanted effects or side effects occur with hydrotherapy?

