### Diagnostic and biometric evaluation procedure

Each patient will undergo a medical examination at the time of admission and a final examination after two weeks of inpatient therapy, in which the general physical state and disease-specific previous medication and therapy will be documented. At the two medical examinations, pain intensity will be measured on a ten-point visual analogue scale, and 1) diagnostic assessment of the affected joint according to the neutral-zero method (hip joint: flexion and extension, internal and external rotation; knee joint: flexion and extension); 2) the timed "up and go" (TUG test) as an indirect assessment criterion of flexion and extension in the affected hip or knee joint; and 3) the body mass index (BMI) will be recorded in the case report form or physician's questionnaire.

**Independently of the doctor**, a standardised questionnaire will be filled out by the patient at the time of admission and after two weeks of inpatient therapy. These questionnaires will be sent to the evaluation centre directly after they are handed in.

The same assessment will be carried out in a telephone interview by the external study centre, ten weeks after the end of inpatient care.

The assessment includes A) the SF-36 test, B) the Lequesne hip or knee questionnaire, C) the AIM-2-SF Scales 2 Short Form, and D) the EQ-5D test.

In addition, each patient will be given a diary for self-reporting during inpatient treatment. This diary will be completed by the patient: it contains the subjective visual analogue scale, the current mental health state scale of the EQ-5 D test, and blood pressure measurements (filled out by the nursing staff) ((Figure 3)).

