### Outcome measures

#### Primary outcome measure

The primary outcome measure will be the pain intensity of the affected joint during inpatient care, as assessed by the patient and the investigator. The patient rates subjective pain intensity in the patient diary on a ten-point visual analogue scale (0 = no pain; 10 = greatest pain imaginable); the doctor also records pain intensity around the affected joint on a ten-point visual analogue scale. The use, practicality, and validity of visual analogue scales have been sufficiently evaluated and are scientifically accepted [30,31]

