#### V) Rating the indirect flexion and extension ability of the hip or knee joint and general patient mobility through the timed "up and go" (TUG) test

In its original form, the TUG is an internationally recognised procedure for rating body balance and the danger of falling during an everyday task involving movement. For this reason, it is a standard procedure in geriatric and general practitioner assessment of individual patient mobility and risk of falling. The TUG's validity, inherent consistency, and reliability are scientifically proved [37]. To carry out the test, the patient sits on a chair with armrests, which is placed three metres from a wall. When prompted, the patient has to stand up, pause in front of the chair, walk the three metres to the wall, turn around without touching the wall, walk back to the chair, turn around again and sit down. The time required, use of aids, and general feasibility are measured. We use the TUG test, together with an estimate of general mobility, to rate flexion and extension of the affected knee or hip joint indirectly, as described previously in the scientific literature for the indication of osteoarthritis [38]. The TUG test will be administered by the investigator at the beginning of the study and again at the end of the inpatient treatment phase

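### For the three scales analysed by repeated-measures ANOVA with a week-12 value, the group-by-time p-value cannot tell a short-lived from a lasting effect, as research question 4 asks

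*Protocol article*

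**What the plan says.** Question 4 under Research questions reads "Do hydrotherapeutic applications simply provide short-term therapeutic success or are there long-term changes in the clinical findings". The abstract gives the schedule: "Assessments will be made at baseline, after two weeks of inpatient treatment, and finally after a further ten weeks of follow-up".

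Not every outcome follows that schedule. Under Diagnostic and biometric evaluation procedure, the questionnaire set is defined ("The assessment includes A) the SF-36 test, B) the Lequesne hip or knee questionnaire", then AIMS2-SF and EQ-5D), and "The same assessment will be carried out in a telephone interview by the external study centre, ten weeks after the end of inpatient care". The other outcomes stop at discharge:

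- Primary pain: "The primary outcome measure will be the pain intensity of the affected joint during inpatient care".
- TUG: "at the beginning of the study and again at the end of the inpatient treatment phase".
- Joint mobility, blood pressure and BMI: inpatient stay only, under their own headings.

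Statistical analysis then states that a repeated-measures ANOVA "will be performed for the longitudinal analysis of the primary outcome measure (VAS), and for the secondary outcome criteria". The list of outcomes that follows mixes inpatient-only variables (VAS, TUG, mobility, blood pressure) with three scales that have a week-12 value: the SF-36 sum scales, AIMS2-SF and the Lequesne index. EQ-5D goes to chi-square tests. Post hoc tests are mentioned only with the one-way ANOVA in the baseline-homogeneity text. No contrast at week 2, at week 12 or between the two is named.

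**The concern.** Question 4 concerns when an effect is present. A repeated-measures ANOVA with three arms and three occasions offers three standard tests:

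- The time term does not compare arms.
- The group term averages over occasions, including admission, where randomised arms should not differ.
- The group-by-time term asks only whether the arms' profiles differ in some way.

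Only the last bears on a treatment effect over time, and it does not say at which visit the arms part. If it is significant, the p-value fits a gain gone by week 12, a gain that appears only by week 12, or a gain held throughout. If the contrasts are chosen after the data are seen, the visit that supports a long-term claim is also chosen after the fact. The Discussion gives the scarcity of evidence on sustained effects as a reason for the trial, so the distinction matters.

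**Working it through.** **Inputs from the protocol:** three arms, 180 patients (abstract; Sample size); three occasions for the scales concerned; repeated-measures ANOVA (Statistical analysis).

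**Assumed, because the article does not give them:** 60 per arm; 5% level; SD 1 at each occasion; one common correlation ρ; complete data; an effect of d SD in one arm and none in the other two, with d from 0.3 to 0.6.

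**The plan's own figure.** The 180 patients at 95% power refer to an interaction on the primary outcome. No effect size, level, correlation or number of measurements is given, so the figure cannot be reproduced. With λ = f²·N·m/(1−ρ) and df (k−1)(m−1) and (N−k)(m−1), it fits f = 0.148 for m = 2 and ρ = 0.5, or f = 0.132 for m = 3 and ρ = 0.5. Only the arm size is used below.

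**Step 1, the test.** df₁ = (3−1)(3−1) = 4; df₂ = (180−3)(3−1) = 354; λ = n·S/(1−ρ), where S is the sum of squared interaction effects. For a profile v in one of three arms, S = (1 − 1/3)·Σ(vₜ − v̄)².

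**Step 2, three patterns at admission, week 2, week 12.**

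- Short-lived (0, d, 0): deviations −d/3, 2d/3, −d/3; sum of squares 6d²/9 = 2d²/3.
- Late (0, 0, d): the same deviations in another order; 2d²/3.
- Lasting (0, d, d): deviations −2d/3, d/3, d/3; 2d²/3.

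So S = (2/3)(2d²/3) = 4d²/9 for all three, and the noncentrality is identical.

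**Step 3, numbers.**

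| d | ρ | λ = 60·(4d²/9)/(1−ρ) | Power, each pattern |
|---|---|---|---|
| 0.3 | 0.5 | 60·0.0400/0.5 = 4.80 | 37.6% |
| 0.5 | 0.5 | 60·0.1111/0.5 = 13.33 | 84.2% |
| 0.6 | 0.5 | 60·0.1600/0.5 = 19.20 | 95.4% |
| 0.5 | 0.7 | 60·0.1111/0.3 = 22.22 | 97.7% |

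**Step 4, simulation** (4,000 runs, d = 0.5, ρ = 0.5). The omnibus test is set beside contrasts of change from admission, affected arm against one other arm, each at an unadjusted two-sided 5%.

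| Pattern | Group-by-time | Week-2 contrast | Week-12 contrast |
|---|---|---|---|
| None | 5.3% | 5.0% | 4.4% |
| Short-lived | 84.4% | 78.2% | 5.3% |
| Late | 83.5% | 5.2% | 78.1% |
| Lasting | 84.1% | 77.7% | 77.9% |

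Hand check of the contrasts: a change score has variance 2(1−0.5) = 1, so the standard error of an arm difference is √(2/60) = 0.183 and d/SE = 0.5/0.183 = 2.74, in line with about 78% power.

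**Step 5, other assumptions.** With arms at 0, 0.3 and 0.6 SD and correlations between 0.5 and 0.6, 3,000 simulated trials per pattern give 93.6% (week 2 only), 91.4% (week 12 only) and 90.5% (both). Exact equality is lost, but a significant result still does not identify the pattern.

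**The case against.** The best reply is that the section names a model family and stops. It does not say that one omnibus test decides, that it spans all three occasions, or that contrasts are excluded. A condensed article may leave follow-up contrasts to a fuller plan, and any omnibus test behaves as shown. This has force: the three-occasion group-by-time test is the natural reading, not stated text. What remains is that the section assigns a specific procedure to these scales, places post hoc tests elsewhere, and has a better method available on the same data.

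Three stronger readings may tempt a reader, and the protocol supports none of them.

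- *The trial leaves question 4 unanswered, or would report a passing benefit as a 12-week effect.* Visit means would show the pattern descriptively, and nothing in the article announces such a report.
- *The flaw affects the primary outcome, since the quoted sentence names the VAS.* Primary pain is defined on inpatient care, so the argument does not reach it.
- *A week-12 contrast alone would settle whether an effect lasts.* The late pattern also triggers that contrast (78.1%). Moreover, all arms receive active treatment, so a null week-12 difference could mean that both arms kept their benefit.

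**Conclusion.** The point holds for three secondary scales: the SF-36 sum scales, AIMS2-SF and the Lequesne index. For these, the only longitudinal test named has the same power for short-lived, late and lasting effects of equal size (84.2% each at d = 0.5 and ρ = 0.5), so its p-value cannot answer question 4. Exact equality rests on the assumed equal allocation, variances, correlations and complete data. The conclusion that the p-value does not locate the effect needs none of these and does not depend on the sample size. The point does not extend to VAS pain, TUG, mobility or blood pressure, nor to EQ-5D. It is a worthwhile change to the analysis wording and not a threat to the primary result.

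**What to change.** In Statistical analysis, for the SF-36 sum scales, AIMS2-SF and the Lequesne index:

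- Estimate from one longitudinal model the between-arm differences at week 2 and at week 12, each adjusted for the admission value, with 95% confidence intervals.
- Name the arm pairs: hydrotherapy versus physiotherapy, and hydrotherapy versus combination (questions 5 and 6). State the order of testing, or declare the contrasts exploratory.
- Base any claim of a long-term between-arm effect on the week-12 contrast. Call an effect lasting only if it is present at both week 2 and week 12.
- Report within-arm change from admission at both visits as descriptive, because a null week-12 contrast between active arms does not show that benefit was lost.

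Cost: no new data or visits, but 2 arm pairs × 2 visits = 4 contrasts per scale, with the multiplicity that brings. If presence is judged by significance, requiring both visits also costs power. In the lasting scenario above, with about 78% per contrast, the chance that both are significant lies between 78 + 78 − 100 = 56% and 78%, before any multiplicity adjustment.

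The change cannot answer question 4 for VAS pain, joint mobility or TUG, which have no week-12 value. The text should say so.

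### Adjustment that depends on an observed baseline imbalance lets the data choose the covariates and gives up precision; baseline VAS should be a covariate in every case

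*Protocol article*

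**What the plan says.** The Statistical analysis section of the protocol article sets out a sequence.

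- **Baseline check.** "To check the homogeneity of the groups, a cross-sectional comparison of the baseline characteristics will be carried out". Metric variables, VAS among them, are compared by one-way ANOVA. For the rest, "The nominal variables sex, affected joint (left, right, both sides) and the items of the EQ-5D will be analysed with chi-square tests".
- **Primary analysis.** "An analysis of variance with measured value repetition (ANOVA, repeated measures) will be performed for the longitudinal analysis of the primary outcome measure (VAS"). Metric secondary outcomes are handled the same way. No baseline covariate is named.
- **Trigger.** "Should, contrary to expectations, there be any inhomogeneity between the groups with respect to important variables (baseline characteristics), adjustments will be made", to the extent feasible, within the longitudinal analysis.

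The section does not say which variables count as important, how large a difference counts as inhomogeneity, or what form the adjustment takes. Nothing in the article commits to adjusting for baseline VAS regardless of the check.

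The section on the diagnostic and biometric evaluation procedure has the investigator record pain on the VAS at the admission examination and at the final examination after two weeks, so a baseline value is already collected. The Primary outcome measure section also includes the patient's own VAS rating in the inpatient diary.

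**The concern.** In a properly randomised trial, baseline differences between arms arise by chance. A homogeneity check therefore cannot tell which covariates belong in the model. A small p-value does not make a variable prognostic, and a large one does not make an imbalance in a prognostic variable harmless. The baseline value of the outcome is usually worth adjusting for because it predicts the later value, whether or not the arms differ on it.

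Two things are at stake. The covariates in the primary model are settled only after the baseline data are seen, with room for judgement over what is important. And in the default case, where no inhomogeneity is declared, the analysis does without precision that the admission VAS would give at no cost.

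**Working it through.** **Inputs from the article.** Three arms and 180 patients in total (Abstract). Power of 95% for the group interaction on the primary outcome (Sample size). Repeated-measures ANOVA of the VAS (Statistical analysis). Investigator VAS at two visits (diagnostic and biometric evaluation procedure).

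**Assumed, because the article does not state them.** Two-sided alpha 0.05; pre-post correlation rho of 0.3, 0.5 and 0.7; equal variance s² at the two visits; for the simulation only, 60 patients per arm.

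**Step 1: the plan's own figure.** The article says that "a sample size of n = 180 patients will suffice to determine a possible interaction between the groups with respect to the primary outcome". This cannot be reproduced, since alpha, effect size, correlation and number of measurements are not given. It can be solved backwards. For a within-between interaction with g = 3 groups and m = 2 measurements, the noncentrality is lambda = f²·N·m/(1−rho), with 2 and 177 degrees of freedom. Power of 95% needs lambda = 15.7, so N = 180 implies f = 0.175, 0.148 or 0.114 at the three correlations. Working forwards, f = 0.15 with rho = 0.5 gives N = 177. The figure is plausible, but f is back-solved and verifies nothing. Below, 95% is taken as given.

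**Step 2: variances.** With two time points, the group-by-time test is the comparison of change scores.

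- Change score: s² + s² − 2·rho·s² = 2s²(1−rho)
- ANCOVA on the discharge value: s²(1−rho²)
- Ratio of ANCOVA to change score: (1−rho²)/[2(1−rho)] = (1+rho)/2

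The direction does not depend on equal variances. With SDs s0 at admission and s1 at discharge, the change-score variance minus the ANCOVA variance is (s0 − rho·s1)², which is never negative.

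**Step 3: effect on power.** Lambda scales with the inverse ratio 2/(1+rho). ANCOVA uses 2 and 176 degrees of freedom.

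| rho | variance ratio | lambda with ANCOVA | power at N = 180 | N for 95% power with ANCOVA |
|---|---|---|---|---|
| 0.3 | 0.65 | 15.7 × 1.54 = 24.2 | 99.5% | about 120 |
| 0.5 | 0.75 | 15.7 × 1.33 = 20.9 | 98.7% | about 138 |
| 0.7 | 0.85 | 15.7 × 1.18 = 18.5 | 97.6% | about 156 |

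The gain over 95% is 2.6 to 4.5 percentage points.

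**Step 4: does the trigger recover the loss?** A simulation (10,000 runs, three arms of 60) applied ANCOVA only when the baseline VAS differed at p < 0.05, and the change-score test otherwise. That threshold is an assumption.

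| rho | power, never adjusted | power, trigger rule | power, always ANCOVA | type I error, trigger rule |
|---|---|---|---|---|
| 0.3 | 65% | 66% | 84% | 4.3% |
| 0.5 | 81% | 82% | 91% | 4.0% |
| 0.7 | 96% | 96% | 98% | 4.7% |

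Power here is for an assumed effect of 0.5 SD in one arm, which is not the article's planning effect. The rule recovers almost none of the lost precision, because it adjusts in only about 5% of trials. Its overall type I error stays below 5%. Within the roughly 5% of null trials with a significant baseline difference in VAS, the unadjusted test rejects 12% to 19% of the time, against about 5% for ANCOVA.

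**The case against.** The strongest reply is that little is lost. Taking the article's 95% power at face value, ANCOVA adds only a few points. The trigger looks at baseline data and not at outcomes, so it offers no direct route to picking a favourable result. The definitions of important variables and of the adjustment could sit in an analysis plan that is not shown. The first two points stand and limit the size of the finding. The third stands for the missing definitions, but the conditional rule is itself the stated method, so the finding does not rest on silence.

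Three stronger readings are tempting, and the documents do not support them.

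- *That the plan inflates false positives or is biased.* Over randomisation the change-score contrast is unbiased, and the rule's overall type I error is about 4% to 5%. Error is raised only conditional on a chance baseline imbalance. One can pick out trials with an unflagged imbalance (difference above 0.5 points, assumed SD 2, baseline p > 0.05; about 12% of two-arm null trials) and find rejection of 8% to 11%. That is a selected slice resting on figures the article does not give.
- *That the trigger is likely to fire by chance.* The section lists at least 17 baseline variables (10 metric, sex, affected joint, five EQ-5D items), and 1 − 0.95^17 = 58% if they are independent. But only important variables count, no p-value threshold is stated, and these scales are correlated. The 58% is not the probability of adjustment.
- *That the variance ratio holds for the whole primary outcome.* It is derived for two time points. If the diary VAS is analysed at more than two, the group-by-time test is no longer a simple change score and these figures do not carry over.

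**Conclusion.** The point holds as one of efficiency and prespecification. As written, the covariates of the primary analysis depend on the observed baseline data through an undefined criterion, and the default model omits the baseline value of the outcome as a covariate. For the investigator's VAS at admission and discharge, ANCOVA would have 65% to 85% of the variance of the planned comparison at correlations of 0.3 to 0.7, and would lift the claimed 95% power to between 97.6% and 99.5%. The loss shrinks as the correlation approaches 1. These sizes rest on assumed correlations, equal variances at the two visits, alpha 0.05, and the article's power claim being true for this test. If the real effect is smaller than planned, the gain in power can be larger, as the simulation shows. A change is worth making because it improves the primary analysis at almost no cost; the validity of the trial does not depend on it.

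**What to change.** Replace the conditional sentence in the Statistical analysis section with an unconditional one: the primary VAS and every other metric longitudinal outcome are analysed with the baseline value of that outcome as a covariate, whatever the baseline comparison shows. With one post-baseline value this is ANCOVA. With several, such as diary ratings, it is a longitudinal model of the post-baseline values with baseline as a covariate. Report baseline characteristics by arm descriptively, without significance tests and without consequences for the model. Hip or knee may be added as a further prespecified covariate; this is optional.

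The cost is one or two sentences. No new data are needed, since the admission VAS is already recorded, and the sample size need not change. The change should be made before the outcome data are examined.
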